#### Secondary endpoints

Secondary analyses will include: (i) a per-protocol analysis based on all participants who have received at least 4 weeks of randomised therapy and (ii) intention-to-treat and per-protocol analyses in the subgroup with “definite” or “definite”/“probable” infection at randomisation. These secondary analyses will focus on consistency of point estimates and 95 % CI, rather than formal comparison with the 7.5 % non-inferiority margin. We will similarly compare the proportions of participants with secondary endpoints, or the distributions of continuous secondary outcomes (rank sum tests). Subgroup analyses will use interaction tests to determine the consistency of treatment effects by type of infection and infecting pathogen. We record treatment intentions for both intravenous and oral routes at baseline before randomisation. Subgroup analysis will compare efficacy of intravenous versus oral antibiotic therapy according to whether or not rifampicin was used as an adjunctive therapy in the intravenous and oral arms (four subgroups). We will also conduct subgroup analyses according to the clinician’s specific antibiotic intentions, as recorded prior to randomisation.

A survival analysis will be performed to assess post-randomisation surveillance bias, which would present as a delay in time to meeting an endpoint in one randomised group. Other secondary analyses will include regression models (logistic (binary) or quantile (continuous)) to calculate estimates of treatment differences for the primary and secondary endpoints adjusted for age, comorbidity, infecting pathogen and type of surgical intervention.

The statistical analysis plan will be locked prior to analyses being undertaken and will be made freely available at the time of publication.

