**Methods:**

The OVIVA trial is a parallel group, randomised (1:1), un-blinded, non-inferiority trial conducted in thirty hospitals across the UK. Eligible participants are adults (>18 years) with a clinical syndrome consistent with a bone, joint or metalware-associated infection who have received ≤7 days of intravenous antibiotic therapy from the date of definitive surgery (or the start of planned curative therapy in patients treated without surgical intervention). Participants are randomised to receive either oral or intravenous antibiotics, selected by a specialist infection physician, for the first 6 weeks of therapy. The primary outcome measure is definite treatment failure within one year of randomisation, as assessed by a blinded endpoint committee, according to pre-defined microbiological, histological and clinical criteria. Enrolling 1,050 subjects will provide 90 % power to demonstrate non-inferiority, defined as less than 7.5 % absolute increase in treatment failure rate in patients randomised to oral therapy as compared to intravenous therapy (one-sided alpha of 0.05).

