If continuing in the randomised strategy (IV or PO) is no longer compatible with optimal clinical care, the clinician must commence appropriate alternative therapy. Appropriate reasons for discontinuing the allocated treatment might include lack of suitable medication within the allocated strategy, adverse reactions, contraindications or susceptibility testing results. Failure to maintain intravenous access is an appropriate reason for discontinuing IV antibiotics. A wound discharge or other clinical signs related to the incident infection, or its apparent resolution, are not appropriate indications for changing from one treatment strategy to the other, since there is equipoise regarding efficacy.

There are no formal withdrawal criteria in this study other than at the request of a participant. All patients are free to withdraw their consent at any time; if they elect to withdraw from the allocated treatment strategy during the randomised treatment phase, they will meet a secondary endpoint but may still be followed up and be included in the analysis provided that appropriate consent is given.

Any medical decision to withdraw a participant from the randomised strategy is discussed with the chief investigator (CI) or the trial physician. Changing the antibiotic whilst remaining within the allocated strategy need not be discussed, but a clinician with appropriate training in managing infection must make such a decision.

The infection specialist may adjust dosage based on renal or hepatic function, drug interactions or other factors according to drug labelling information, the British National Formulary and local pharmacy guidelines. All antibiotics used (including dosage, route of administration and duration) are recorded from the day of randomisation through to final follow-up at one year (Fig. 1).

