### Sample size

The sample size estimation of 1,050 was based on an anticipated overall failure rate of 5 %, as suggested by short-term follow-up in the single centre pilot study, and a non-inferiority margin of 5 % (a relative increase of 100 %), with a one-sided alpha = 0.05, 90 % power and 10 % loss to follow-up.

Pooled data from a planned interim analysis demonstrated that the true event rate is likely to be closer to 12.5 %. To account for this, we adjusted the non-inferiority margin to 7.5 % (a relative increase of 60 %). As the final control group failure rate remains unknown, recruitment will continue as planned until October 2015 to achieve the largest possible sample size within the original target, and to optimise the potential utility of subgroup analyses. The DMC and ethics committee approved this amendment.

Sample size calculations for binary outcomes were performed in Stata (StataCorp LP, College Station, TX, USA).

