### Analysis of efficacy

#### Primary endpoint

Based on intention to treat, the proportions of participants experiencing the primary endpoint at one year follow-up (definitive treatment failure as adjudicated by a blinded ERC) will be tabulated by treatment administration group (that is, PO versus IV therapy). If the absolute, upper 90 % confidence interval around the unadjusted difference (oral versus intravenous) is less than 7.5 %, then the criteria of non-inferiority will be met.

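### The 4-week per-protocol rule can exclude participants because they failed early, which may bias this supportive analysis in either direction

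*Protocol article*

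**What the plan says.** All references are to the protocol article.

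- **Per-protocol set** (Analysis of efficacy, Secondary endpoints): "a per-protocol analysis based on all participants who have received at least" 4 weeks of randomised therapy. No exception is stated for participants who fail before week 4. Item (ii) of the same list adds per-protocol analyses in the subgroups with definite, or definite or probable, infection.
- **Role of the analysis** (same section): the results are read for consistency of point estimates and 95% confidence intervals, "rather than formal comparison with the 7.5 % non-inferiority margin".
- **Primary analysis** (Primary endpoint): "Based on intention to treat, the proportions of participants experiencing the primary endpoint at one year follow-up" are compared between the arms.
- **Endpoint window and treatment period** (Abstract, Methods): the endpoint is "definite treatment failure within one year of randomisation", and allocated therapy is given "for the first 6 weeks of therapy".
- **Leaving the route** (Study interventions): "If continuing in the randomised strategy (IV or PO) is no longer compatible with optimal clinical care, the clinician must commence appropriate alternative therapy". The same section says that clinical signs of the incident infection are not appropriate grounds for changing strategy, and names loss of venous access as an acceptable reason to stop IV therapy.

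**The concern.** The endpoint window opens at randomisation, but entry to the per-protocol set is decided by what happens over the following 4 weeks. If a participant fails in that time and treatment is stopped or moved to the other route, the failure itself is the reason for exclusion. The set is then selected partly on the outcome it is meant to compare.

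In a non-inferiority trial the per-protocol result is the usual check on whether departures from allocated treatment have diluted a real difference. Here its stated use is consistency with the intention-to-treat estimate, so a distorted point estimate undermines exactly that use: agreement could reassure falsely, and disagreement would be hard to interpret. The per-protocol subgroup analyses inherit the same rule.

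**Working it through.** **The plan's own figures.** The article gives no figure for the per-protocol set. Its sample size reproduces: 5% v 10%, "with a one-sided alpha = 0.05, 90 % power and 10 % loss to follow-up", pooled-variance formula without continuity correction, gives 474 per arm, 948 in total, and 948/0.9 = 1,054 against the stated 1,050. This confirms how the inputs are read; the point does not depend on it.

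**Inputs from the article.** Failure rate 12.5% and margin 7.5 points (Sample size), so a true difference at the margin is 12.5% v 20%.

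**Assumed inputs.** The article does not give the shares excluded. Let f be the share of an arm's one-year failures removed by the 4-week rule, and w the share of its non-failures removed. I take w = 10% in both arms and vary f from 5% to 30%. If leaving the route had nothing to do with failing, f would equal w. An excess of f over w represents failure prompting exit.

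**Formula.** Per-protocol failure rate in an arm with true rate p:

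p(1−f) / [p(1−f) + (1−p)(1−w)]

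With w = 10%, the non-failure term is 0.875 × 0.9 = 0.7875 for IV and 0.80 × 0.9 = 0.72 for oral.

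**IV arm (p = 0.125)**
- f = 5%: 0.11875 / 0.90625 = 13.1%
- f = 10%: 0.1125 / 0.9000 = 12.5%
- f = 20%: 0.1000 / 0.8875 = 11.3%

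**Oral arm (p = 0.20)**
- f = 10%: 0.18 / 0.90 = 20.0%
- f = 20%: 0.16 / 0.88 = 18.2%
- f = 30%: 0.14 / 0.86 = 16.3%

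**Per-protocol difference, oral minus IV (true difference 7.5 points)**

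| Failures excluded, IV / oral | Difference (points) |
|---|---|
| 10% / 10% | 7.5 |
| 20% / 20% | 6.9 |
| 10% / 20% | 5.7 |
| 5% / 20% | 5.1 |
| 10% / 30% | 3.8 |
| 20% / 10% | 8.7 |

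Three patterns follow.

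1. When failures and non-failures are lost in equal proportion in both arms, there is no bias.
2. When failures are lost more often than non-failures, equally in both arms, the difference shrinks without any asymmetry. If no non-failures are removed (w = 0), it is 0.1800/0.9800 − 0.1125/0.9875 = 7.0 points at f = 10%, and 0.1600/0.9600 − 0.1000/0.9750 = 6.4 points at f = 20%.
3. When the arms differ in f, the bias follows the arm that loses more failures: towards no difference if that is oral, away from it if that is IV. If the arms are truly equal at 12.5%, the 5%/20% case gives 11.3% − 13.1% = −1.8 points, and the mirror image gives +1.8.

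**Scale.** With 525 per arm (1,050/2), the standard error of the difference at 12.5% v 20% is √(0.125×0.875/525 + 0.20×0.80/525) = 2.27 points, so the 95% half-width is about 4.4 points. The illustrated shifts run from −3.7 to +1.2 points. They are within sampling error but large enough to alter a reading of consistency.

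**The case against.** A reader might infer something stronger: that the rule removes more early failures from the oral arm and so pushes the analysis towards non-inferiority. The mechanism is plausible in an open-label trial. An early oral failure can be moved to IV, whereas an early IV failure can stay on IV, and the Discussion itself expects open-label bias to favour IV. But the documents do not establish it.

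- Study interventions rules out clinical signs of the incident infection as grounds for switching, and the Discussion says the short IV allowance in the oral arm is not meant as rescue for the bone infection. A participant who fails but stays on the allocated route for 4 weeks remains in the set.
- Departures from IV are also foreseen, through loss of access, and the Discussion reports that many patients asked for oral therapy. Gastrointestinal intolerance and poorer adherence point to departures from oral. Which way these move the estimate depends on whether those leaving are failures. If IV loses 20% of its non-failures against 10% in the oral arm, with f = 10% in both, the IV rate is 0.1125/0.8125 = 13.8% and the difference 6.2 points. If IV loses more of its failures, the difference rises instead.
- The 5%/20% case needs IV failures to leave less often than IV non-failures, and nothing in the article quantifies that.

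It can also be said that the consequence is limited. The decision is made on intention to treat, where early failures are counted; early termination of therapy is a reported secondary endpoint; and the per-protocol result is not tested against the margin. This stands, although Diagnostic subgroup definitions says that secondary analysis will evaluate non-inferiority in the infection subgroups, which sits uneasily with the consistency-only reading.

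Finally, the analysis plan, which is not shown, may already treat early failures properly. That is possible, but the article states the membership rule itself, and as stated it makes no exception.

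Early death needs separate treatment. Under Outcome measures death is a secondary endpoint, so excluding someone who dies before week 4 without definite failure does not remove a primary event.

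**Conclusion.** The point holds in limited form. The per-protocol set is conditioned on an event that early failure can prevent, so some participants may be excluded because of their outcome. This can bias the supportive per-protocol estimate, and its subgroup versions, in either direction. Bias towards no difference is plausible, but the article gives neither the share of failures before week 4 nor the share who would leave the route.

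Under the assumed shares, a true 7.5-point difference appears as anything from 3.8 to 8.7 points, and is unchanged when failures and non-failures are lost alike. These figures illustrate sensitivity and are not predictions. The primary conclusion is untouched, so this is a worthwhile clarification of a secondary analysis and not a defect that must be cured for the trial to answer its question.

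**What to change.** Redefine the per-protocol set as participants who stayed on the allocated route for at least 4 weeks or until adjudicated definite failure, if earlier. Exclude only those who left the route before week 4 while free of definite failure. Report participants who die on the allocated route before week 4 without definite failure separately, or vary their handling in a sensitivity analysis. Tabulate exclusions by arm and reason. Use the same definition in the per-protocol subgroup analyses.

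This removes exclusion caused by the endpoint itself. It does not restore a randomised comparison, because those who leave the route free of failure may still differ between arms; the table of exclusions lets a reader judge that.

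The cost is one or two sentences before the analysis plan is locked. No new data are needed: antibiotic use by route and duration is recorded from randomisation, endpoints are under prospective surveillance, and the planned survival analysis already requires failure times.

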### Outcome measures

Endpoints are identified by prospective surveillance throughout the year post-randomisation.

The primary endpoint is definite failure of infection treatment, where definite failure is indicated by one or more of the following:Isolating bacteria from two or more samples of bone/spine/peri-prosthetic tissue, where the bacteria are phenotypically indistinguishableIsolating a pathogenic organism (for example, *Staphylococcus aureus,* but not *Staphylococcus epidermidis*) on a single, closed biopsy of native bone or spineDiagnostic histologic findings on bone or peri-prosthetic tissueFormation of a draining sinus tract arising from bone or prosthesisRecurrence of frank pus adjacent to bone or prosthesis.

Secondary endpoints are:Serious adverse events (SAEs), including death (that is, all-cause mortality)IV line complications (infection, thrombosis or other events requiring early removal or replacement of the line)“Probable” or “possible” treatment failure, as composites with definite treatment failure. These are determined by blinded endpoint committee review and defined by the presence of any one of the following criteria:Loosening of a prosthesis, confirmed radiologicallyNon-union of a fracture after 6 months, confirmed radiologicallySuperficial spreading erythema, treated as cellulitis with an antibiotic for >1 week; where results from deep tissue samples do not meet the primary endpoint as described above

Where appropriate deep tissue samples have been sent for microbiology and results of the culture are negative, and any of a), b) or c) are met, then the endpoint will be regarded as “possible”. On the other hand, where deep tissue samples are not sent for microbiology, and any of a), b) or c) are met, then the endpoint will be regarded as “probable”4.Early termination of the planned 6-week period of oral or IV antibiotic therapy because of adverse events, patient preference or any other reason5.Resource allocation determined by: a) length of inpatient hospital stay; b) frequency of outpatient visits; or c) antibiotic prescribing costs6.Quality of life evaluated by EQ-5D-3 L questionnaire7.Oxford Hip and Knee Scores (where infection is in the hip or knee)8.Adherence to oral medication.

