### Health economic analysis

The health economic evaluation has two parts. The first, a within-trial analysis, will be performed based on the resource use and health-related quality of life (EQ-5D-3 L) data. We will use the British National Formulary for antibiotic costs (with a sensitivity analysis for hospital pharmacy discounts). We will include the costs associated with IV administration based on staffing requirements, equipment cost, clinic visits and transport costs for patient visits as observed in the trial. For unplanned inpatient stays and additional outpatient attendances other than those related to IV administration, we will use standard NHS reference costs.

We will calculate mean costs in each arm of the trial and differences in costs between the two arms, with 95 % confidence intervals. The EQ-5D-3 L instrument will be used to estimate per-patient quality-adjusted life years (QALY) with adjustment for any differences between the groups in EQ-5D-3 L at baseline. Non-parametric bootstrapping techniques will be employed to confirm the robustness of the statistical analysis of cost, QALY and cost per QALY. Uncertainty in cost-effectiveness will be represented on the cost-effectiveness plane and as confidence intervals for cost-effectiveness ratios, or as cost-effectiveness acceptability curves, as appropriate.

The second part of the analysis will be to extrapolate the observed results in OVIVA beyond the clinical trial, in order to explore the potential lifetime cost-effectiveness of a switch in antibiotic administration route strategy. This extrapolation will be made in each diagnostic group, using estimates of long-term recurrence from the literature and the observed recurrence rates observed within the period of the trial. We will also use the published longer term costs associated with disability in order to reflect the consequences of treatment failure that persist beyond the end of the trial. Taking these estimates together, we will extrapolate the costs beyond the period of observation within the year of follow-up in the trial. This will necessarily involve a series of assumptions in applying estimates from the literature, and extensive sensitivity analyses will be examined in order to explore the robustness of the estimates.

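### The clinical EQ-5D-3L comparison leaves out the baseline score, which the economic analysis collects and adjusts for; the tests stay valid but lose precision

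*Protocol article*

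**What the plan says.** The Outcome measures section of the protocol article lists two patient-reported scales among the secondary endpoints: "Quality of life evaluated by EQ-5D-3 L questionnaire" and "Oxford Hip and Knee Scores (where infection is in the hip or knee").

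The Secondary endpoints section, under Analysis of efficacy, fixes two analyses for continuous outcomes. The first is an unadjusted comparison: proportions for binary endpoints, "or the distributions of continuous secondary outcomes (rank sum tests"). The second is "regression models (logistic (binary) or quantile (continuous)) to calculate estimates of treatment differences for the primary and secondary endpoints", with the models "adjusted for age, comorbidity, infecting pathogen and type of surgical intervention". That list has four covariates, and the baseline value of the outcome is not among them.

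The Health economic analysis section treats the same instrument differently. Quality-adjusted life years are estimated from EQ-5D-3L "with adjustment for any differences between the groups in EQ-5D-3 L at baseline". No section extends that adjustment to the clinical comparison. The Randomisation section names site as the only stratification factor, so baseline quality of life is not balanced by design.

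**The concern.** A score measured before treatment usually predicts the same score measured afterwards. Including it in the model removes variance that has nothing to do with the route of administration, and it corrects for whatever baseline difference chance has produced. Here the baseline EQ-5D-3L is already in the dataset and is used in one analysis but not in the other.

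The abstract puts an improved patient experience first among the expected benefits of oral therapy, and the Discussion relies partly on patient questionnaires to compare the burdens of the two routes. What is at stake is the sharpness of that evidence: a wider interval than necessary, and an estimate that still carries any baseline imbalance that happens to arise.

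**Working it through.** **Inputs from the article.** Target of 1,050 and 10% loss to follow-up (Sample size); 1:1 allocation (abstract, Methods); the analysis methods and covariate list set out above; baseline EQ-5D-3L available (Health economic analysis).

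**Assumptions, not in the article.** Baseline-to-follow-up correlation ρ of 0.3 to 0.7; 1,050 × 0.9 / 2 ≈ 472 analysed per arm; a difference of 0.2 SD for illustrating power; two-sided 5% tests; equal SD in both arms.

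**1. The plan's own figure.** The article gives no precision or power figure for quality of life. Its only sample size is for the primary endpoint. A one-sided test of 5% against 10% at alpha 0.05 and 90% power gives 474 per arm, or 948 in total. Then 948 / 0.9 ≈ 1,054, close to the stated 1,050. That figure serves here only to set the number per arm.

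**2. Precision.** In SD units, the SE of the unadjusted difference is √(2/472) = 0.065. Adjusting for baseline multiplies the variance by 1 − ρ², and the equivalent sample-size factor is 1/(1 − ρ²). Unadjusted power for 0.2 SD is 86.7%.

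| ρ | 1 − ρ² | Variance cut | Sample-size factor | Adjusted SE | Power for 0.2 SD |
|---|---|---|---|---|---|
| 0.3 | 0.91 | 9% | 1.10 | 0.062 | 89.6% |
| 0.5 | 0.75 | 25% | 1.33 | 0.056 | 94.4% |
| 0.7 | 0.51 | 49% | 1.96 | 0.047 | 99.0% |

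At ρ = 0.7 the variance falls to 51% of its unadjusted value, a cut of 49%.

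**3. Chance imbalance.** Suppose the arms differ at baseline by 1.96 SE, that is 1.96 × 0.065 ≈ 0.128 SD. The unadjusted follow-up difference then shifts by ρ × 0.128 = 0.038, 0.064 or 0.089 SD. Given that imbalance, the test statistic has mean 1.96ρ and variance 1 − ρ², so the chance of a false positive is 7.9%, 12.9% or 20.5%. Averaged over all randomisations it stays near 5%: simulated rank-sum rates under no effect were 4.9%, 4.0% and 5.0%.

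**4. A score shaped like EQ-5D-3L.** The formula in step 2 is for means, so it was checked by simulation on a skewed score with a ceiling (472 per arm, underlying effect 0.2 SD).

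| ρ | Rank-sum power | Power of rank-based analysis adjusted for baseline | Fall in SD of median-regression estimate when baseline is added |
|---|---|---|---|
| 0.3 | 83% | 87% | about 6% |
| 0.5 | 86% | 93% | about 18% |
| 0.7 | 87% | 99% | about 33% |

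Power is from 2,000 replicates and the SDs from 200. A separate run of 1,500 replicates at ρ = 0.3 gave a plain linear model with baseline less power than the rank-sum test (80% against 85%).

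**5. Gain over the planned models.** Steps 2 to 4 compare baseline adjustment with no adjustment. Against quantile models that already hold four covariates, the relevant quantity is the partial correlation of baseline with follow-up. To the extent that those covariates share information with the baseline score, the gain is smaller than shown. The article does not allow it to be calculated.

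**The case against.** The strongest reply is that one covariate list serves every model, binary and continuous. A baseline score has no meaning for treatment failure or line complications, so a shared list would naturally omit it, and the statistical analysis plan could add it for the patient-reported scales. That is possible, and it is why the point is small. But the article names its covariates rather than leaving them open, and followed as written it gives a less precise EQ-5D-3L comparison than the collected data allow.

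The article also does not say whether the outcome is a follow-up value or a change from baseline. The precision argument holds either way. With equal variances, a change score has variance 2(1 − ρ) relative to the follow-up score, that is 1.4, 1.0 or 0.6 at ρ = 0.3, 0.5 or 0.7, against 0.91, 0.75 or 0.51 with baseline as a covariate. The uncorrected shift in step 3 of the working applies to follow-up values.

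Several stronger readings are tempting but not supported:

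- A reader might infer that chance imbalance could drive the result. It could not in general. The error rate holds over randomisations, and even a 1.96 SE imbalance moves the difference by less than 0.1 SD.
- A reader might infer that the plan gives no effect estimate because rank-sum tests give none. The quantile models are there to provide one.
- A reader might infer that the Oxford scores lose most, since they cover only hip and knee infections. The article documents no baseline Oxford score.
- A reader might infer that a repeated-measures model for mean differences is needed. For a skewed score with a ceiling, rank and quantile methods are defensible, and in the simulation at ρ = 0.3 a linear mean model did worse.
- A reader might infer that the clinical and economic results will conflict. A QALY and a score distribution are different quantities and may differ however baseline is handled.

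**Conclusion.** The point holds as a minor improvement in efficiency. The article fixes an EQ-5D-3L analysis without the baseline score while using that score in the economic evaluation. Nothing in it makes the planned tests invalid. The loss is one of precision, together with an uncorrected shift if an imbalance is observed. Its size depends on a correlation that the article does not give: negligible to modest near 0.3, substantial near 0.7, and somewhat less in both cases when measured against the covariate-adjusted models. It concerns a secondary endpoint only.

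**What to change.** Before the statistical analysis plan is locked, add one sentence: the main EQ-5D-3L comparison will be the planned quantile regression with the baseline EQ-5D-3L score added to the named covariates, reported as a treatment difference with its 95% confidence interval, and the rank-sum test will be supportive. Apply the same to the Oxford Hip and Knee Scores only if a baseline score is held. Rank-sum tests can stay as they are for outcomes with no baseline, such as length of stay.

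No new EQ-5D-3L data are needed and the code is routine. The cost is that participants without a baseline score need a standard missing-baseline approach, stated in advance so that they are not dropped from the comparison. The planned models are already conditional on covariates, so the interpretation of the estimate changes little.
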